### Recruitment and participants

All obstetricians and gynecologists of the Montreal area were contacted with the help of the Collège des Médecins du Québec and were asked to distribute brochures to women who meet the inclusion criteria. Advertisements were also placed on Facebook and articles were published in the university paper and on several specialized blogs. Recruitment will continue until 60 pregnant women have joined the study, 30 in the exercise group and 30 in the control group.

Inclusion and exclusion criteria were chosen to minimize individual differences among participants and to ensure the women’s safety (see Table1). Participants will be withdrawn from the study if exclusion criteria are met during the course of the study or if they withdraw their consent.

**Table 1 T1:** Inclusion and exclusion criteria for the Healthy Mom, Bright Child study

**Inclusion criteria**	**Exclusion criteria**
First trimester of pregnancy	Use of alcohol, cigarettes or illegal drugs
20 to 35 years of age	Health complications
Pre-pregnancy body mass index between 18 and 25	Unable or unwilling to breastfeed
No known health conditions	Excessive or insufficient weight gain (25 to 35 lbs according to pregnancy weight gain recommendations) [24]
Use of folic acid	Non-compliance with the experimental protocol

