### Procedure and timeline

Women will join the study prior to their 13^th^ week of pregnancy to receive the intervention during the entire second and third trimesters. Gestational age will be determined from the menstrual history. During the first meeting, women will be informed that they will be randomly assigned to the active or control group. Study design is presented in Figure1. They will be clearly informed of the characteristics of each group and of what is expected of them. To avoid any auto-selection bias, they will be assigned to a group only after they have provided their informed consent.

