### General information questionnaire

During the first visit, all participants will be asked to answer questions regarding their and their partner’s professional, economic, educational and health status as well as a family history of hereditary disorders. This questionnaire also documents the details of the participants’ pregnancy.

Monthly visits will include a follow-up questionnaire that will inquire about their health and general habits (for example, alcohol consumption, massages, acupuncture) to ensure they remain eligible to participate in the study as well as to document potential confounders between the two groups.

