### Medical records

A copy of the complete medical records will be obtained from each woman’s obstetrician at the postnatal visit to verify weight gain and standard pregnancy blood test results as well as details of the delivery.

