### Preliminary results

As of September 2011, 17 women have given their consent and been randomly assigned to one of the two groups: nine in the exercise group and eight in the control group. Two women from the exercise group and three from the control group were excluded: two for having a miscarriage, one for being pregnant with twins, one for not complying with the experimental protocol, and one for withdrawing consent. Table2 presents the characteristics of all participants.

**Table 2 T2:** Participant characteristics

	**Active group**	**Control group**
	**(n = 7)**	**(n = 5)**
Age (years)		
Mother	29 ± 3	28 ± 4
Father	31 ± 4	31 ± 6
Pre-pregnancy body mass index	24.9 ± 3.7	27.9 ± 5.8
Pre-pregnancy KPAS index	11.62 ± 1.39	10.93 ± 0.65
First trimester KPAS index	9.71 ± 1.19	8.97 ± 1.39
Mother	3 (3)	5 (5)
Father	5 (7)	3 (3)
Revenue ($)	80,000 to 100,000	60,000 to 80,000
(median class)	(40,000)	(40,000)

Data presented as the mean ± standard deviation, except for Education and Revenue, which are presented as the interquartile range. KPAS: Kaiser Physical Activity Survey.

Preliminary results indicate that all women completed the online daily log from week 13 until birth. The active women (n = 7) had journal entries for 23 to 28 weeks and exercised an average of 3.1 ± 0.9 days per week. Sessions lasted from 20 to 90 minutes, at an intensity ranging from 12 to 15 on the Borg scale. Activity type included aerobics, swimming, tennis, elliptical training, hiking, circuit training, Wii sports and rollerblading, with the most common being walking, cycling and water aerobics. Women in the control group (n = 5) had journal entries for 24 to 27 weeks and exercised an average of 0.8 ± 0.6 days per week. Sessions lasted from 20 to 40 minutes, at an intensity ranging from 12 to 13 on the Borg scale. Activities included cycling, water aerobics and swimming, walking being by far the most common.

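### Withdrawing women whose weight gain falls outside 25 to 35 lbs selects after randomisation on a variable that exercise may change; the effect is uncertain and probably modest

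*Protocol article*

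**What the plan says.** Table 1 of the protocol article puts this in the exclusion column: "Excessive or insufficient weight gain (25 to 35 lbs according to pregnancy weight gain recommendations". The text above the table makes the column operative after entry: "Participants will be withdrawn from the study if exclusion criteria are met during the course of the study". The reason given is that "Inclusion and exclusion criteria were chosen to minimize individual differences among participants", together with the women's safety.

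Under Procedure and timeline, women join and are assigned before week 13 so as "to receive the intervention during the entire second and third trimesters". A monthly questionnaire serves "to ensure they remain eligible to participate in the study" (General information questionnaire). The obstetric record is obtained "at the postnatal visit to verify weight gain" (Medical records).

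Under Preliminary results, of 17 women randomised, "Two women from the exercise group and three from the control group were excluded". The reasons were miscarriage (two), twins, non-compliance and withdrawn consent; none was weight gain. Table 2 then describes only the remaining 7 and 5. Nothing in the article keeps a withdrawn woman in the analysis.

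**The concern.** A range for total pregnancy gain cannot work as an entry screen in the first trimester. The 35 lb ceiling can be crossed before term, but the 25 lb floor is settled only near the end. Monthly visits cannot decide a total that is still building up.

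The rule therefore sorts women on something measured after months of assigned exercise or no exercise. If exercise lowers gain, it removes more low gainers from the active group and more high gainers from the control group. Those who stay then differ in whatever underlies weight gain. That undercuts the statement under Methodological strengths that randomisation will make the groups comparable.

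A second cost is numbers. The sample size section allows 30% attrition, and losses for other reasons already stand at 5 of 17 (29%).

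**Working it through.** **The plan's own figure.** Inputs from Sample size calculations: difference 50%, SD 56%, type I error 0.05 (taken as two-sided), power 80%. Standardised difference d = 50/56 = 0.893. The two-sample t-test needs 20.7, so 21 per group (power 80.6%). With 30% attrition, 21/0.70 = 30. Both stated figures reproduce.

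**Timing.** Assume linear gain over 40 weeks. The share after week 13 is 27/40 = 68%. A woman ending at 30 lbs passes 25 lbs at week 40 × 25/30 = 33.3; one ending at 25 lbs reaches it only at birth.

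**What the early data allow.** The article reports: "Preliminary results indicate that all women completed the online daily log from week 13 until birth". Of these 12 women, none was removed for weight. The one-sided 95% upper limit is 1 − 0.05^(1/12) = 0.221. The chance of seeing none of 12 is 0.90^12 = 0.28 at a true rate of 10%, and 0.80^12 = 0.07 at 20%. The bound is soft for two reasons. Record checks may have been pending. Table 1 may also not have been applied strictly: mean pre-pregnancy BMI among the controls kept was 27.9 (Table 2), against a limit of 25.

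**Power.** The observed loss to other causes leaves 30 × 12/17 = 21.2 per group. Weight withdrawals are taken as additional.

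| Further loss to weight | n per group | Power at d = 0.893 |
|---|---|---|
| 0 | 21.2 | 0.809 |
| 10% | 19.1 | 0.765 |
| 20% | 16.9 | 0.712 |
| 22.1% | 16.5 | 0.700 |

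**Bias.** The documents give no distribution of gain, no effect of exercise on it and no link with the MMN, so all three are assumed. Control gain is normal with mean 30 + k/2. Exercise subtracts k lbs. Both arms are cut to 25–35 lbs, with the SD set so that 10% or 20% fall outside. The bias in SD units of amplitude is (difference between retained arms in the gain they would have had without exercise) × correlation / SD of gain.

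| k (lbs) | Outside range | SD of gain (lbs) | Difference, active − control (lbs) | Bias, correlation 0.3 |
|---|---|---|---|---|
| 2 | 10% | 2.87 | 0.68 | 0.071 |
| 2 | 20% | 3.77 | 1.08 | 0.086 |
| 4 | 10% | 2.33 | 0.88 | 0.113 |
| 4 | 20% | 3.31 | 1.84 | 0.166 |

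With correlation 0.1 the range is 0.024 to 0.055; with 0 it is 0. The largest value is 0.166/0.893 = 19% of the planned effect. The women kept in the active arm are those with the higher underlying gain, so the bias takes the sign of the correlation: it favours exercise if gain and amplitude rise together, and works against it otherwise.

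**A wider spread.** With mean gain 28 to 34 lbs, SD 8 to 12 lbs, a shift of 0 to 4 lbs and correlation 0 to 0.4 (all assumed), the bias is 0 to 0.18 SD, much the same. Retention under strict enforcement would be only about 29% to 47% per arm. At 47% retained, none of 12 removed would have probability 0.47^12, about 0.0001, so the early data do not suggest strict enforcement with that spread.

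**The case against.** The strongest case is about weight of evidence. Every input to the bias range is assumed, and the narrow SDs are solved back from an assumed share outside the range. The one-fifth figure is a maximum only over the inputs chosen. The only data show no withdrawal for weight. The power loss adds a hypothetical figure to 5 of 17, whose exact 95% interval runs from 10% to 56%, and the 30% allowance may have been meant to cover weight withdrawals too. All of this stands and limits the point to an uncertain, probably modest effect. It does not change the fact that the rule is written down and selects after randomisation.

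The criteria also serve safety, and the 35 lb ceiling can be crossed while exercise continues. But health complications remain a separate criterion, and exercise can be stopped on medical grounds without removing the woman from the study. Once final gain is known, withdrawal protects nobody. The aim of reducing individual differences is met by limits applied before randomisation, such as age and BMI.

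The analysis population may be defined in a document not shown, and the source of the 25 to 35 lb range cannot be consulted. Reading it as a whole-pregnancy total is natural but is still a reading. Finally, removal for non-compliance is tied more directly to the assigned behaviour and stays in force, so this change alone does not restore the groups as randomised. That also stands.

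**Conclusion.** The concern holds. Table 1 and the withdrawal sentence together remove women on a variable that becomes known after randomisation and exposure and that exercise may plausibly change; the last part is inference. The likely harm is minor to moderate. Power falls to about 76% or 71% if weight costs a further 10% or 20% on top of other losses, and to 70% at the upper limit the early data allow. Bias runs from zero to about 0.17 SD under the assumptions in the main scenario. It vanishes if exercise does not shift gain or if gain is unrelated to the MMN. The stated sample size is not wrong. The change is worth making because it is cheap and recruitment is still open; confidence is medium because no documented figure fixes the size.

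**What to change.** Delete the weight-gain line from the exclusion column of Table 1. Add under Recruitment and participants: *Gestational weight gain will not lead to withdrawal or to exclusion from the analysis; total gain will be reported by group.* Test and analyse these mother–infant pairs as randomised, and use the postnatal record only to complete the data. An analysis limited to 25 to 35 lbs may be kept if labelled exploratory. Whether to keep removing women for non-compliance needs its own decision.

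The cost is a minor amendment cleared with the ethics committee and applied to women already randomised. On the reported figures none needs reinstating, and no visit or measurement is added. The downside is slightly more variation in weight gain, which may add some variance to the MMN.

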### Procedure and timeline

Women will join the study prior to their 13^th^ week of pregnancy to receive the intervention during the entire second and third trimesters. Gestational age will be determined from the menstrual history. During the first meeting, women will be informed that they will be randomly assigned to the active or control group. Study design is presented in Figure1. They will be clearly informed of the characteristics of each group and of what is expected of them. To avoid any auto-selection bias, they will be assigned to a group only after they have provided their informed consent.

**Figure 1 F1:**
[figure not shown]
Study design.

Two interventions will be offered: individual recommendations on health habits during pregnancy; and individual recommendations on exercising during pregnancy. To ensure that each group has similar knowledge about health habits during pregnancy and that there is the same amount of one-on-one contact with all participants, both groups will receive the first intervention. Only the active group will receive the second intervention, recommending at least three sessions of exercise per week (see section on Exercise intervention). Participants in the control group will not be given any exercise counseling and will be informed they will be excluded from the study if they exercise more than once per week.

Starting at the beginning of the second trimester, all women will complete a daily log and wear a pedometer for the entire duration of the study. Women from both groups will meet monthly with the same kinesiologist and will receive standardized advice and feedback based on their daily log. During that meeting, all the women will complete a mood questionnaire and the women who are part of the active group will complete an exercise session in order to learn how to characterize their at-home exercise for the daily log. The women who are part of the control group will complete the same exercise session but only once per trimester. During each trimester women from both groups will fill out a three-day nutrition journal and during the second and third trimesters they will wear an accelerometer and a Polar heart rate monitor for seven days and three nights. The timeline of the experimental protocol is presented in Figure2.

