### Measurements

#### Exercise intensity

Participants in the exercise group will perform a supervised exercise session on a cycle ergometer every month (Corival, Lode B.V., Groningen, The Netherlands) to learn the use of Borg’s perceived exertion scale. To allow the participants to easily identify the minimal intensity required for their at-home exercise, target intensity will correspond to 12 on the Borg scale (that is, 55% of their VO_2_max). The entire session will last 30 minutes, including a 5 minute warm up and a 5 minute cool down. Participants in the control group will be asked to complete a similar supervised session once per trimester to allow them to measure intensity in the event that they do exercise.

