### Mood questionnaires

Animal studies on the effect of exercise during pregnancy on the newborn’s brain suggest that a high level of maternal anxiety diminishes this effect [12]. Therefore, during their monthly visit, the women will be asked to fill out the Beck Anxiety Inventory [32].

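### The protocol says one-on-one contact is equal in both arms, but only visit frequency, provider and log feedback are matched; supervised-session time and exercise counselling are not

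*Protocol article*

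**What the plan says.** Under Procedure and timeline (the text after Figure 1), the protocol article names two individual interventions: advice on health habits and advice on exercising. It gives a reason for sharing the first one, namely that both arms should know the same about health habits and that "there is the same amount of one-on-one contact with all participants".

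The text that follows separates the arms: "Only the active group will receive the second intervention, recommending at least three sessions of exercise per week". For controls it adds: "Participants in the control group will not be given any exercise counseling".

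The same section has all women see the same kinesiologist every month, complete a mood questionnaire and get standardised feedback on their daily log. The supervised exercise session differs. Under Exercise intensity, "Participants in the exercise group will perform a supervised exercise session on a cycle ergometer every month", and the session is set at 30 minutes. For the other arm, Procedure and timeline says: "The women who are part of the control group will complete the same exercise session but only once per trimester".

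**The concern.** Equal contact is presented as something the design achieves, and a reader would take it as a control for attention and support. Sharing one of two individual interventions cannot equalise contact when the other goes to one arm only. The supervised sessions then add to the difference at most monthly visits.

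The protocol has its own reason not to dismiss this. Under Mood questionnaires it notes that animal studies "suggest that a high level of maternal anxiety diminishes this effect". It therefore accepts that the mother's state may alter the effect on the newborn, and extra professional support is one thing that might influence that state.

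The Discussion intends to draw conclusions about physical exercise itself and to inform the advice given to pregnant women. No measurement described in the article records contact time, and the Methodological weaknesses section does not mention the difference. If the equal-contact statement were carried into the trial report, readers would be told that a source of difference had been removed when it had not.

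**Working it through.** The plan gives no figure for contact time, so there is none to reproduce. The check has two parts.

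**1. What is matched and what is not**

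| Element | Active | Control | Matched? |
|---|---|---|---|
| Health-habits intervention | yes | yes | yes |
| Monthly meeting, same kinesiologist, log feedback | yes | yes | yes |
| Mood questionnaire at the monthly visit | yes | yes | yes |
| Individual exercise counselling | yes | no | no |
| 30-minute supervised session | every month | once per trimester | no |

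The first four rows come from Procedure and timeline. The last comes from that section and Exercise intensity.

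**2. Size of the difference in supervised-session time**

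Inputs:
- Session length: 30 minutes (Exercise intensity).
- Follow-up in the active arm: 23 to 28 weeks of log entries (Preliminary results).
- Active sessions: at about 4.35 weeks per month, 23 / 4.35 = 5.3 months and 28 / 4.35 = 6.4 months. I assume 5 to 7 sessions.
- Control sessions: one per trimester. I assume 2 if only the second and third trimesters count, and 3 if a first-trimester session also takes place.

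Formulas: minutes = sessions × 30; difference = (active − control sessions) × 30; ratio = active / control sessions.

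| Active sessions | Control sessions | Active min | Control min | Extra min | Ratio (session time only) |
|---|---|---|---|---|---|
| 5 | 3 | 150 | 90 | 60 | 1.7 |
| 5 | 2 | 150 | 60 | 90 | 2.5 |
| 6 | 3 | 180 | 90 | 90 | 2.0 |
| 6 | 2 | 180 | 60 | 120 | 3.0 |
| 7 | 3 | 210 | 90 | 120 | 2.3 |
| 7 | 2 | 210 | 60 | 150 | 3.5 |

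No combination gives equality. Exercise counselling, of unstated length, comes on top in the active arm.

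**Why the ratio does not carry over to total contact.** Let the shared part of each visit last S minutes, a figure the article does not give. With 6 visits, the ratio is (180 + 6S) / (60 to 90 + 6S).
- S = 30 (assumed): 360 / (240 to 270) = 1.3 to 1.5.
- S = 60 (assumed): 540 / (420 to 450) = 1.2 to 1.3.

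The ratio depends on an unknown. The extra session minutes do not.

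**The case against.** The strongest reply is that contact is matched where it matters. Both arms have the same number of visits with the same person, and feedback is standardised. The extra half hour is cycling at the target intensity, done so that women can rate their exercise at home. It is therefore largely exercise and its delivery, not separate social support. Exercise counselling is the randomised contrast itself, and withholding it from controls is intended. Anxiety, one route by which contact could act, is measured monthly in both arms and compared under Statistical analyses. The outcome is a newborn EEG measure, which extra attention to the mother is less likely to affect directly than it would a self-report.

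Most of this stands, and it rules out two stronger readings.

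- A reader might infer that no effect could be attributed to exercise. The documents do not support that. Most of the added time is exercise, and the randomised comparison of the programme with control is unaffected.
- A reader might infer that the active arm has two to three times as much contact. That ratio describes supervised-session minutes only. The length of the first meeting and of the shared part of each visit is not given in the text.

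The anxiety remark also has limits: it reports what animal studies suggest, and does not say that kinesiologist contact changes anxiety.

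The reply does not rescue the statement itself. Equal visit counts are not an equal amount of contact, and measuring anxiety does not show how much contact each arm had.

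**Conclusion.** The concern holds in a limited form. The equal-contact statement conflicts with the schedule in the same section and with Exercise intensity. Visit frequency, provider and log feedback are matched. Supervised-session time and exercise counselling are not.

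The active arm has about 60 to 150 more minutes of supervised session per woman. This rests on assumed counts of 5 to 7 and 2 to 3 sessions; the 30 minutes is stated. The upper control count needs a first-trimester session, which falls before the period used to count the active sessions. Dropping it would widen the gap. Figures 1 and 2 were not available to this review, so any visit lengths shown there are not reflected.

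The consequence is for interpretation. The trial can estimate the effect of the exercise programme as delivered, including its counselling and supervised sessions. It cannot claim to have held contact equal. No sample size, endpoint, test or allocation changes.

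**What to change.** 1. Replace the equal-contact statement under Procedure and timeline with: *visit frequency is matched; supervised-session time and exercise counselling are not.*
2. Have the kinesiologist record contact minutes at each existing visit in both arms, and report them by arm. By September 2011, 17 of the planned 60 women had been randomised and recruitment was continuing, so most could still be covered. The report should say from when the minutes were recorded.
3. Word the conclusion as the effect of the exercise programme including its counselling and supervised sessions, and list the contact difference under Methodological weaknesses.

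Cost: a corrected sentence, one field on the visit form, and a slightly narrower claim. No visit is added and neither arm's schedule changes.
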